## Abstract

**Background:**

Seasonal influenza has an estimated global reach of 3-5 million infections, with 290,000-650,000 influenza-related deaths yearly. Despite its efficacy in reducing morbidity and mortality, influenza vaccination rates remain low globally and in South Africa. Youth between the ages of 18 and 34 years are not prioritized for influenza vaccines although influenza surveillance in South Africa shows that individuals aged 19-44 years present the highest asymptomatic episodes and the lowest medically attended illness. This creates an opportunity to investigate if and how vaccine demand can be created in the absence of clear imperatives to vaccinate. The study tests the effectiveness of tailored, context-specific education, and community engagement, including community and social media to increase influenza vaccination uptake. Tailored, context-specific education, community engagement, reliable vaccine supply, and free, localized access are all critical for improving perceptions of, increasing confidence in, and motivating the uptake of vaccination.

**Objective:**

This study will explore strategies to increase influenza vaccine uptake amongst economically marginalized youth aged 18-34 years in Soweto (South-Western Townships), South Africa, where influenza vaccines are not universally accessible through the public health system for this age group.

**Methods:**

The Bambisana Study uses an innovative approach, including community influencers and social media to increase the uptake of influenza vaccines through designing and testing an integrated communications strategy targeted at economically marginalized youth in Soweto, South Africa. The study uses a mixed methods pretest-posttest intervention design to test the effects of the interventions. The intervention will consist of the following components: (1) social media campaign, (2) microinfluencers on and offline, and (3) nonsocial media focused, offline microinfluencer-led engagement within communities. Quantitative data will be collected using a randomized household sample pre- and posttests, and clinic surveys with vaccinees and clinic attendees who declined vaccination. Focus group discussions (FGDs) will be conducted pre- and post intervention with participants aged ≥18 years, and 20 key informant interviews (KIIs) will be conducted with key influencers including religious leaders, traditional healers, and youth leaders. FGDs and KIIs will be audio-recorded and transcribed into English for analysis using framework thematic analysis, and quantitative data analyses will be conducted using SAS Enterprise (Guide 7.15; SAS Institute).

**Results:**

This study was funded in December 2022, with recruitment having started in May 2023. As of May 2024, all data collection is complete, with data analyses and preparation of peer-reviewed publications in progress. The first results are expected to be submitted for publication in November 2024.

**Conclusions:**

Enhancing perceptions of, bolstering confidence in, and fostering uptake of vaccination relies heavily on the efficacy of yearly influenza vaccination initiatives, personalized education tailored to specific contexts, active community involvement, consistent vaccine availability, and easily accessible, cost-free distribution channels at the local level.

**International Registered Report Identifier (IRRID):**

DERR1-10.2196/60481

## Introduction

Globally, seasonal influenza causes an estimated 3-5 million infections, and 290,000-650,000 deaths annually [1,2]. Estimates for the influenza burden of disease are limited in Africa; however, hospitalization and mortality are higher in low- and middle-income countries (LMICs) than in high-income countries [3,4]. In South Africa, an estimated 6,000-11,000 people die from influenza every year, with approximately half of these deaths in older individuals, and people living with HIV [5]. Seasonal outbreaks of influenza pose challenges to the health care system, leading to increased hospitalizations, outpatient visits, and strain on health care resources [6]. Vulnerable populations, including the older individuals, young children, pregnant women, and individuals with underlying medical conditions are at the highest risk of severe infection [7].

While nonpharmaceutical interventions can play a role in decreasing influenza infections, vaccination is deemed pragmatic and endorsed by the World Health Organization (WHO) as the recommended method for preventing seasonal influenza [1]. Overall, vaccine efficacy to prevent influenza infection ranges from 40% to 60%, with higher vaccine efficacy (82%) in reducing severe illness and hospitalization [8,9]. Therefore, the influenza vaccine is especially recommended for those who have chronic illnesses, those who are pregnant, and older individuals [10-12]. Influenza vaccination campaigns typically prioritize these groups during the influenza vaccination season [7,13]. However, an investigation into the seasonal influenza burden in urban and rural areas in South Africa showed that children younger than 12 years and those aged 19 and 44 years have an elevated risk of acquiring seasonal influenza [14]. Whilst severe disease is less likely, vaccinating younger adults has the added indirect benefit of providing herd immunity to the family and communities [15,16]. Furthermore, vaccination offers potential economic benefits related to the out-of-pocket expenses incurred by patients to treat influenza-related symptoms. An estimated annual cost of US $111.3 million is incurred by the government, while out-of-pocket costs incurred by the patient were reported to be US $40.7 million [17]. Individuals are at risk of financial loss due to absence from work and missed opportunities for those who are self-employed [18]. Despite recommendations, seasonal influenza vaccine uptake in the most vulnerable groups is low in LMICs, including South Africa [19]. Accessibility, lack of knowledge, and risk perception have been cited as the most significant barriers to vaccination in South Africa [20].

Despite the demonstrated effectiveness of vaccines in significantly reducing morbidity and mortality of affected individuals, youth are less proactive in health care–seeking behaviors due to low-risk perception and are not necessarily encouraged to vaccinate for influenza and other infectious diseases [9,21-23]. For COVID-19, youth were not initially prioritized for vaccination rollout, yet they might have been in contact with vulnerable populations [24,25]. In addition, evidence suggests that low vaccination rates are in part due to low health care–seeking behaviors among youth. Health care–seeking behaviors are the actions involved in achieving and maintaining a healthy condition [26,27]. Various factors, both individual and related to health care providers, can influence young people’s health care–seeking behaviors [28].

Targeted health promotion interventions can increase health care–seeking behaviors and uptake of vaccination [29]. Influenza surveillance shows that individuals aged 19-44 years present the highest asymptomatic episodes and the lowest medically attended illness [14,30]. Studies undertaken in sub-Saharan Africa have shown that leveraging community involvement in immunization programs positively contributes to vaccine confidence and uptake [31,32]. In the case of HIV, for example, awareness campaigns to lower the burden of HIV and AIDS epidemics in Southern African countries have proven vital in reducing the rise of the disease [33]. The use of television series to promote positive sexual health and prevent HIV effectively engaged the youth by challenging old models of education [34]. The use of social media campaigns has also been increasingly used to promote behavior change [35,36] while sparking debate, especially when considering the abundance of false and misinformation [37]. It is vital to consider the significance of social media to improve vaccine uptake in LMICs.

Promoting health care through various platforms and to youth in LMICs may improve vaccination uptake. Therefore, as part of the Bambisana Project, which includes a diverse and multidisciplinary team comprising social and behavioral scientists, biostatisticians, population health surveillance specialists, health communications researchers, community influence and engagement practitioners, and marketing and communication strategists, we aim to:

Evaluate the impact of influencers online, offline, and in collaboration, on influenza vaccine uptake, with a specific focus on young people, and assess the additional value added by social media engagement.Design and implement an integrated communications strategy centered around community influencers and social media to increase the uptake of influenza vaccines, particularly among younger populations who are likely unemployed, partially or informally employed, and living in Soweto (South-Western Townships), South Africa.Explore motivations and barriers to health priorities, and to influenza vaccination, through the use of microinfluencers both online and offline in Soweto, South Africa.

The outcomes of the project will include increased influenza vaccination rates at the local health care clinics linked to campaign interventions, alongside an improved attitude toward the importance of vaccination in the target audience—this will be assessed using the Vaccine Confidence Index scale [38] and measured against the most recent Vaccine Confidence Index data from South Africa [39]. In addition, the project will provide important health systems-strengthening recommendations, which could potentially be implemented within the current infrastructure.

## Methods

### Research Design

The primary research aim uses a prospective mixed methods study design, including qualitative and quantitative data collection, to assess the effects of community and social media interventions to increase influenza vaccine uptake among youth in Soweto, South Africa. During the intervention phase, surveys will be conducted among potential participants attending study clinics who accepted or declined influenza vaccination.

### Study Setting

The study will be conducted in Soweto, which is a congregation of 29 townships within the Johannesburg Metropolis in South Africa [40]. Soweto is one of the poorest areas of Johannesburg with high rates of youth unemployment which is at 46.3% among the 15- to 34-year age group [41].

### Sampling

The Bambisana Project leverages the Soweto Health and Demographic Surveillance System, led by Wits Vaccines and Infectious Diseases Analytics Research Unit since 2017 and part of the Child Health and Mortality Prevention Surveillance Programme. The Soweto Health and Demographic Surveillance System has been providing access to longitudinal health and demographic data for specific enumerated areas of Soweto and the South of Johannesburg, since 2017 [42]. The study population includes young adults aged 18-34 years from four Health Demographic Surveillance System (HDSS) economically marginalized and geographically distinct Soweto communities namely Phiri, Senaoane, and Mapetla, Mofolo and Meadowlands, Thulani, and neighboring Thembelihle. Adults (18 y and older), living in these clusters or accessing clinic services in the following five study clinics: Senaoane Clinic, Mofolo Community Health Centre, Meadowlands Zone 2 Clinic, Siphumlile Clinic, and Thembelihle Clinic are deemed eligible for the study. Table 1 below shows the population of HDSS communities that will comprise our study clusters while Figure 1 presents the study design.

**Table 1 table1:** Health and Demographic Surveillance System (HDSS) cluster summary data.

Cluster number	Communities	Total population	Youth 18-34 years	Number of households with youth	Total number of households
Cluster 1	Mofolo and Meadowlands	20,986	5824	3478	5912
Cluster 2	Phiri, Senaoane and Mapetla	23,805	6801	4037	6626
Cluster 3	Thulani	23,711	6848	4072	6262
Cluster 4	Thembelihle	19,449	5648	3831	6586

**Figure 1 figure1:**
[figure not shown]
Project timeline: data points and study design. Flu: influenza; FGD: focus group discussion.

### Community Engagement

The Bambisana (an isiZulu word, which means to work together) study leverages active, long-standing, dynamic community-level relationships and partnerships in accessing community insights at the household and local clinic level. The Wits Vaccines and Infectious Diseases Analytics social behavioral sciences team has longstanding relationships through Community Advisory Boards (CAB) and extensive community engagement in support of health research objectives throughout Soweto. CAB members are individuals residing in the HDSS-enumerated areas, who have been identified as active citizens in their communities. There are standing quarterly CAB meetings with the study team and members; however, these often increase in relation to shifting project activities. Consultations span project development, implementation, and community feedback sessions at the end of data collection, analysis, and interpretation.

### Formative Qualitative Data Collection

The qualitative component includes 16 focus group discussions (FGDs) stratified by age group (18-24 y and 25-34 y), sex (male and female) and community (2 per cluster). These approaches aim to gather contextual data essential for understanding the factors influencing young people’s decisions regarding influenza vaccination, including both motivators and barriers.

Study staff will purposively select and recruit young people for FGDs and key stakeholders from the community for key informant interviews (KIIs). FGD recruitment will be iterative until data saturation is achieved [43]. All study participants will be recruited through the CAB members who work with HDSS communities. Trained and experienced qualitative researchers fluent in local languages spoken in Soweto and Thembelihle (including isiZulu and Sesotho) will conduct the qualitative research using the participants’ language of choice. The FGDs (16 FGDs; 8-12 participants per FGD) and KIIs (20; 10 male and 10 female participants) will be audio-recorded after written informed consent is obtained.

### Intervention

The intervention will be delivered through a public health messaging campaign in targeted clusters or “subplaces” in Soweto, leveraging microinfluencers to provide information and motivate positive attitudes toward vaccination without a mandate in currently unvaccinated populations. The aim of the campaign is to create a behavioral change action: to go to your local clinic to get vaccinated. This has the secondary aim of highlighting the extent to which such intervention might be possible on wider issues of public health in the future. Secondary to this is the desire to investigate the value-add of social media targeting wider forms of engagement, such as that which occurs in communities offline.

The campaign will be timed with points when the clinic is well-supplied and prepared for such a public drive. The project will mitigate the risk of potential vaccine shortages by making vaccine donations to partner clinics. The study will center around the 2023 national influenza vaccination drive. Vaccines are generally provided in a very short and sporadic supply to the local community clinics, so supplying vaccines is also a part of the objective to make a community-level impact as part of the project.

The implementation of the intervention will be guided by information obtained after conducting community engagement discussions, which would be used to design the messaging and communication strategy. Surveys will be administered before, during, and following the communication interventions to establish baseline, midline, and end-line measures for evaluating the intervention’s impact. This will help assess the effectiveness of four distinct approaches aimed at boosting influenza vaccine uptake among youth across clinics in four diverse HDSS clusters.

Standard of care: Vaccine made available with standard government promotional activity without support from the project (ie, based on standard government drive).Social media: Social media campaign pushed to the target audience to highlight availability and drive to get vaccinated.Microinfluencers on and offline: The social media campaign will be amplified through a coordinated effort by microinfluencers in their online and offline networks.Offline microinfluencers: Nonsocial media focused; offline microinfluencer-led engagement within communities.

The intervention components are detailed below:

1. Social media campaign to highlight availability and drive to get vaccinated pushed to the target audience (18-34 y) in 4 distinct geographic areas. Using Meta platforms Facebook and Instagram, along with other relevant social media channels identified through community engagement and marketing insights, we will disseminate information through static images, carousel posts, and video posts to promote the availability of, education around, and motivation to get vaccinated. Paid advertising on Meta will target people aged 18-34 years in two of the four distinct geographic study clusters.

2. Microinfluencers on and offline: the social media campaign will be amplified through a coordinated effort by microinfluencers in their online and offline networks. We will use community influencers—people with traditional influence such as community leaders, religious leaders, elders, and key business leaders—to amplify our social media campaign. They will engage their online and offline networks in coordination with our social media campaign to promote vaccine availability and encourage vaccination.

3. Nonsocial media offline microinfluencers: nonsocial media focused; offline microinfluence led engagement within communities. In these communities, our community influencers will focus only on offline engagement and will be specifically instructed to not do anything on social media. Using interpersonal conversations, and small-scale community events to share the importance of vaccines, they will encourage people to get vaccinated.

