#### Statistical Analysis Plan

We will use descriptive statistics to describe study variables including knowledge of influenza vaccines, experiences with influenza vaccines, stigma, and vaccine confidence. Reliability assessments using the Cronbach alpha test will be evaluated for scale measures. Scales with poor reliability scores will be calibrated using factor analysis. Data will be analyzed overall and stratified by community. Frequencies will be determined for categorical measures whereas means (SD) and medians (IQR) will be determined for continuous measures. Pairwise comparisons of categorical measures between communities will be evaluated by the chi-square or Fisher exact test as appropriate. Similarly, pairwise continuous measures will be analyzed by the 2-sample *t* test, if satisfying normality distribution conditions or the Wilcoxon Mann-Whitney test, if nonnormally distributed. Normality will be assessed by the Shapiro-Wilks method. Drivers of knowledge, stigma, and experiences of influenza vaccines will be determined by logistic regression for binary outcomes and linear regression for continuous outcomes. Multivariable analysis will be carried out to adjust for potential confounders. Model fit statistics will be assessed on all multivariable regression models to ensure the validity of the findings. Data analyses will be conducted using SAS Enterprise (Guide 7.15; SAS Institute) [50].

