## Discussion

### Principal Findings

This study will provide critical insights for improving the effectiveness of influenza vaccination campaigns in South Africa. Leveraging micro- and nanoinfluencers on social media, and collaboration with community influencers has been proven to reach and motivate target groups with low vaccine uptake [51]. This study will provide valuable insights into the use of microinfluencers online and offline to reach economically marginalized communities to make positive health decisions where the personal risk perception from not doing so is low in the absence of any mandated reasons to do so. It will also provide an assessment of the differing impact of campaign approaches and the value of the amplification of voices into online social networks for health outcomes.

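### The most natural reading is one cluster per approach, which confounds approach with community, so the design cannot support the stated claims of effectiveness and differing impact

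*Protocol article*

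**What the plan says.** The Intervention section of the protocol article says the surveys before, during and after the campaign will help "assess the effectiveness of four distinct approaches aimed at boosting influenza vaccine uptake among youth across clinics in four diverse HDSS clusters". The first approach listed is the comparator: "Standard of care: Vaccine made available with standard government promotional activity without support from the project". The other three are a social media campaign, microinfluencers working on and offline, and microinfluencers working offline only. The offline approach is assigned by community: "In these communities, our community influencers will focus only on offline engagement".

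On the reach of social media, the component list in the same section makes two statements. The campaign is "pushed to the target audience (18-34 y) in 4 distinct geographic areas", and then "Paid advertising on Meta will target people aged 18-34 years in two of the four distinct geographic study clusters".

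The Statistical Analysis Plan section gives the between-community analysis: "Pairwise comparisons of categorical measures between communities will be evaluated by the chi-square or Fisher exact test as appropriate". Continuous measures get a two-sample t test or a Wilcoxon test, and regressions adjust for potential confounders. The section names no cluster-level unit.

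The comparative claim returns under Principal Findings: "It will also provide an assessment of the differing impact of campaign approaches". The Background and Methods parts of the Abstract also describe the study as testing effectiveness and intervention effects.

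**The concern.** A campaign is delivered to a community, not to a person. If each approach runs in one community, every difference between approaches is also a difference between two places, and nothing in the data separates the two explanations. Tests on individual respondents count people as the independent units. They answer whether two particular communities differ, not whether one campaign works better than another. More respondents per community make the first answer sharper and leave the second untouched.

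At stake is the first aim in the Introduction: the impact of influencers online, offline and combined, and the value added by social media. Ordinary variation between communities could be published as a campaign effect.

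**Working it through.** **Inputs from the article.** Four approaches including standard of care (Intervention). Four clusters (Table 1). At least 100 households per community approached for the household survey, with minimum totals of 400 pretest and 400 posttest (Sampling, under Quantitative Data Collection). At least 100 young vaccinees per community in the clinic survey (Pre- and Posttest Surveys). The article gives no ICC, cluster autocorrelation, power or effect size, so the ICC and autocorrelation values below are assumptions.

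**Stated sample size.** 4 communities × 100 = 400 per round; 400 × 2 rounds = 800. This reproduces the stated minimum.

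**Replication.** Degrees of freedom for between-cluster variation within approach = clusters − approaches = 4 − 4 = 0. This depends on the one-to-one reading but on no assumed ICC. With 0 degrees of freedom, neither confounder adjustment, GEE nor a mixed model can separate approach from community. The smallest two-sided permutation p-value at cluster level is 2/C(2,1) = 1.0 for one cluster against one. Pooling two clusters with paid social media against two without gives 2/C(4,2) = 2/6 = 0.33.

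**Single-round comparison of two communities, m = 100.** Design effect DE = 1 + (m − 1) × ICC. True type I error of a nominal two-sided 5% test = 2 × [1 − Φ(1.96/√DE)].

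| Assumed ICC | DE | True type I error |
|---|---|---|
| 0.005 | 1.495 | 10.9% |
| 0.01 | 1.99 | 16.5% |
| 0.02 | 2.98 | 25.6% |
| 0.05 | 5.95 | 42.2% |

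A beta-binomial simulation of the chi-square test, at prevalences of 10%, 30% and 50%, gave 16.5–17.6% at ICC 0.01, 25.7–27.1% at 0.02 and 41.7–44.3% at 0.05.

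**Difference in pre-post change between two communities, m = 100, ICC 0.02.** With cluster autocorrelation r, and respondents treated as independent between rounds, true variance over naive variance is f = 1 + m × ICC × (1 − r)/(1 − ICC). The error is 2 × [1 − Φ(1.96/√f)].

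| Assumed r | f | True type I error |
|---|---|---|
| 0.5 | 1 + 100 × 0.02 × 0.5/0.98 = 2.02 | 16.8% |
| 0.8 | 1 + 100 × 0.02 × 0.2/0.98 = 1.41 | 9.9% |
| 0.9 | 1 + 100 × 0.02 × 0.1/0.98 = 1.20 | 7.4% |

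The pre-post contrast reduces the inflation but does not remove it. What remains is community-specific change over time. The Intervention section itself describes clinic supply as short and irregular, plans vaccine donations to partner clinics and times the campaign to periods of good supply. Supply can therefore move uptake in one community and not in another.

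**The case against.** The strongest reply has four parts.

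- **Allocation.** A reader might infer that the article assigns each approach to exactly one cluster. It does not say so: no allocation table is printed and the design figure is not available here. The two statements on social media reach conflict, and the Bias Correction section plans phased delivery, so part of the contrast may be in time. This stands, and one-to-one remains an inference. It does not rescue the comparison, because four clusters cannot give four approaches adequate replication under any allocation. If social media did reach all four areas, the standard-of-care and offline-only contrasts would be contaminated as well.
- **Role of the tests.** A reader might infer that the pairwise community tests are the declared tests of effectiveness. The Statistical Analysis Plan section does not say that. The variables it names are knowledge, experiences, stigma and vaccine confidence; uptake is only to be tracked in the four clusters. This also stands. Yet these are the only between-community tests given, and nothing limits the comparison of approaches to description.
- **Magnitude.** A reader might take 11% to 42% as the error rate of this study. It is not. It belongs to a single-round comparison under assumed ICCs, while the stated design is pretest-posttest in the same households.
- **Supporting evidence.** Exposure questions, uptake tracking and triangulation with qualitative data are already planned. They help interpretation but add no clusters.

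Deferring to a fuller analysis plan does not answer the point, because no analysis can supply replication that the design lacks.

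**Conclusion.** The point holds under the natural reading of one cluster per approach. Approach is then completely confounded with community, with 0 degrees of freedom for between-cluster variation, and the claims to test effectiveness and to assess differing impact go beyond what the design can show. This conclusion needs no assumed ICC.

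The error rates are illustrations only: about 11% to 42% for a single-round comparison at ICC 0.005 to 0.05, and about 7% to 17% for a pre-post contrast at ICC 0.02 with autocorrelation 0.9 to 0.5.

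A reader might also infer that pre-post change relative to the standard-of-care community restores a causal comparison. It does not, because that is still one cluster against one cluster. The matter should be settled before results are published: data collection is complete, so clusters cannot be added, but interpretation can still be corrected.

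**What to change.** 1. State which cluster received which approach, and reconcile the two statements on where social media was delivered.
2. State that approach is confounded with community.
3. Report within-community pre-post changes, and differences in change between communities, as estimates for these four communities. Label individual-level intervals as excluding between-community variation, and interpret no p-value as a test of approach effectiveness.
4. Replace the effectiveness and differing-impact wording in the Abstract, Intervention and Principal Findings with exploratory, hypothesis-generating wording.
5. Use the timing of clinic uptake and reported exposure as supporting evidence only, not as a basis for causal wording.
6. If an ICC sensitivity table is added, state its ICC and autocorrelation as assumptions and match it to the contrast reported. The single-round factor √(1 + (m − 1) × ICC) does not fit pre-post contrasts.

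The cost is a less favourable conclusion and a little more analysis work. No new data are needed.
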